## Abstract

**Background:**

Early restitution of electroencephalogram (EEG) slow wave activity (SWA) may be able to predict favorable functional outcome after cardiac arrest. SWA can be monitored using the C‐Trend Index, a recently developed dynamic numerical index computed using commercially available medical device software.

**Methods:**

This is a pre‐planned prospective substudy of the randomized controlled Sedation, TEmperature and Pressure after Cardiac Arrest and REsuscitation (STEPCARE) trial. With a factorial design, the STEPCARE trial evaluates the effects of three different interventions (sedation, temperature management, and mean arterial blood pressure) on functional outcomes in adult out‐of‐hospital cardiac arrest (OHCA) patients. We will record continuous EEG (cEEG) starting as early as possible after ICU admission. We will compare the accuracy (the proportion of correct predictions of all predictions) of C‐Trend Index with that of blinded retrospective visual analysis of cEEG at 12 h after return of spontaneous circulation in predicting favorable functional outcome (modified Rankin Scale 0–3) 6 months after cardiac arrest. We aim to recruit 300 patients to show noninferiority in prognostic accuracy of the C‐Trend Index compared with the visual analysis of cEEG, using a 2% limit for noninferiority. Furthermore, we will assess whether the therapeutic intervention related to sedation, carried out as a part of the STEPCARE trial modifies the performance of the EEG‐based predictors.

**Conclusion:**

The study will compare the accuracy of SWA measured using C‐Trend Index with the gold standard, visual analysis of cEEG, in predicting favorable functional outcome after OHCA. The study will also assess the effect of the sedation intervention of the STEPCARE trial on the predictive accuracy of C‐Trend Index. If the accuracy of the C‐Trend Index is non‐inferior to the comparator's, it may provide a feasible and easy‐to‐learn bedside method, especially in hospitals with limited availability of neurophysiology expertise.

**Trial Registration:**

ClinicalTrials.gov identifier: NCT06564675

## Background and Significance

1

Guidelines recommend electroencephalography (EEG) assessment after cardiac arrest as a part of the multimodal neuroprognostication of functional outcome [1, 2]. The application of EEG in post‐resuscitation care is often limited by the restricted availability of experts with adequate training to initiate recordings and interpret results during office hours [3].

Traditionally, recommendations have mainly focused on prognosticating unfavorable outcome after cardiac arrest, but recently predicting favorable outcomes has gained attention in recommendations [4]. Early indicators of favorable outcome deserve more attention as they might support, for example, shortening of the sedation after cardiac arrest potentially leading to earlier discharge from the intensive care unit.

Several specific EEG features, such as early return of continuous and normal‐voltage background activity, are often indicative of a favorable outcome, and may thus provide valuable prognostic information already during the first 24 h in the intensive care unit (ICU) [5, 6, 7, 8, 9]. In a Finnish two‐centre study, we recently found that EEG slow wave activity (SWA) during the first 24 h is a promising measure for outcome prediction after cardiac arrest in patients sedated with propofol [10]. In that study, we used C‐Trend Index, a parameter provided by a commercially available medical device software, as a measure of SWA. SWA is a normal feature in EEG during physiological sleep and medical sedation, which supports the assumption that it is associated with normal brain function and favorable outcome after cardiac arrest [11].

Patients with unfavorable functional outcomes had significantly lower SWA during the early phase continuous EEG monitoring (cEEG) compared to those with a favorable functional outcome. A C‐Trend Index below a cutoff value of 20 had the best accuracy for predicting unfavorable outcome before 12 h after cardiac arrest, with a specificity and sensitivity of 95% (83%–100%, 95% Confidence interval) and 83% (70%–92%), respectively. The recordings were performed using a disposable, self‐adhesive frontal electrode and a wireless recording device, eliminating the need for qualified EEG technicians or specially trained nurses [10].

Here, we present the design and rationale behind the PROPEA STEPCARE, which will compare the ability of the C‐Trend Index to predict favorable functional outcomes at 6 months after cardiac arrest with the gold standard, visual analysis of EEG.

Previous studies indicate that improvement of the C‐Trend‐Index beyond a certain cutoff value or improvement of cEEG pattern to a nearly continuous normal‐voltage background at an early time point after cardiac arrest predicts favorable outcome [10, 11, 12, 13].

Our primary objective is to compare the early predictive accuracy of C‐Trend Index cutoff value 20 with blinded retrospective visual analysis of cEEG in predicting favorable functional outcome at 6 months after cardiac arrest. Furthermore, we will assess the effect of the depth of sedation on the predictive ability of cEEG and C‐Trend Index. Comparing minimal sedation with deep sedation is one of the three interventions carried out as part of the STEPCARE trial [14]. The effect of sedation on the predictive ability of cEEG has been identified as a knowledge gap in the recent international consensus recommendation [4].

We hypothesize that the accuracy of the C‐Trend Index is non‐inferior in predicting favorable outcomes at 12 h after return of spontaneous circulation (ROSC) compared to a retrospective visual analysis of cEEG, blinded to the studied therapeutic intervention and outcome, and that the accuracy will not be impaired by the sedation intervention.

## Methods

2

We will report the study according to the Standards of Reporting of Diagnostic Accuracy Studies (STARD) guidelines [15]. The PROPEA STEPCARE is a prospective observational substudy of the Sedation, Temperature and Pressure after Cardiac Arrest and Resuscitation (STEPCARE) trial, a prospective randomized multi‐centre trial with a factorial design. STEPCARE assesses the effects of three different interventions (minimal or deep sedation, temperature management with a device targeting ≤ 37.5°C or conservative management without a device, target level of MAP > 65 or > 85 mmHg) on mortality and functional outcome of adult patients with an out‐of‐hospital cardiac arrest (OHCA) with a non‐traumatic cause [14, 16, 17, 18].

### Patient Population

2.1

The study population is comprised of patients participating in the STEPCARE trial. The study will be conducted in 5–8 selected centres with access to equipment for registering cEEG using the BrainStatus device (Bittium, Oulu, Finland). We will include adult OHCA patients with sustained ROSC, who remain comatose after resuscitation (no response to verbal commands or Full Outline of UnResponsiveness score motor response < 4), and who have no limitations of care. Patients with trauma or hemorrhage as the reason for arrest, patients with suspected or confirmed intracranial hemorrhage, pregnant patients, and those previously randomized to STEPCARE will be excluded [14, 16, 17, 18]. Patients with known allergy to adhesive material and/or injured skin in the frontal‐temporal area preventing the use of the adhesive electrode will be excluded.

### Outcomes

2.2

Functional outcome will be assessed at 6 months follow‐up by an investigator blinded to EEG data and trial interventions [14, 16, 17, 18]. Favorable outcome will be defined as modified Rankin Scale (mRS) 0–3 and unfavorable outcome as modified Rankin Scale 4–6.

### Ethics

2.3

The consent for the STEPCARE trial includes EEG assessment in the multimodal prognostication, regardless of the type of recording. The protocol of the STEPCARE trial, including a deferred consent policy, has been approved by the ethics board of Helsinki University Hospital (HUS/17543/2022) and all other participating sites. All patients are treated according to the Declaration of Helsinki and its later amendments. The Finnish Medical Authority waived the need for a specific permission regarding device research.

### Primary Study Question

2.4

Is the accuracy of the C‐Trend Index non‐inferior to the blinded retrospective visual analysis of cEEG in predicting favorable outcomes of cardiac arrest patients at 12 h after ROSC?

### Secondary Study Question

2.5

Is the accuracy of C‐Trend Index and visual analysis of cEEG in predicting favorable outcome affected by the sedation intervention of the STEPCARE trial?

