The C‐Trend Index values are calculated offline after the recording. The parameter is provided by C‐Trend (Cerenion, Oulu, Finland), a CE‐marked medical device software that utilizes artificial intelligence to capture several power and connectivity features in producing the C‐Trend Index. The parameter ranges from 0 to 100 in values, with higher values referring to higher normal SWA seen during propofol sedation. The parameter is not displayed on the bedside monitor and is not used during the clinical review of the cEEG data. Thus, all clinical and research personnel are blinded to the C‐Trend Index. A running 1‐h average value of the C‐Trend Index is automatically calculated, and for the analysis, the value is picked for each patient from the same time location used in the visual analysis of cEEG.

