### Statistical Analysis Plan and Data Analysis

2.9

Descriptive statistics with categorical values will be presented as numbers and percentages and continuous values with means with standard deviations (SD) or medians with interquartile ranges (IQR).

The sample size is calculated with regard to the primary outcome, that is the comparison of the prognostic accuracy of the C‐Trend Index and the visual assessment of cEEG at 12 h from ROSC as a reference standard. Firstly, we chose the expected sensitivity and specificity based on the study by Admiraal et al. [12], from which Sandroni et al. [13] calculated sensitivity (63.2%) and specificity (82.1%) for a favorable outcome for EEG with continuous or nearly continuous background with normal voltage, at 12 h from ROSC. Expecting a favorable outcome prevalence of 50%, the accuracy of 72.7% was calculated. The estimated accuracy of the C‐Trend Index used for the calculation was 86.08%, based on our previous work [10]. Accuracy stands for the number and percentage of correctly classified patients, calculated according to a formula (TP + TN)/(TP + TN + FP + FN), where TP and TN stand for the number of true positives and true negatives, respectively, and FP and FN stand for the number of false positives and false negatives, respectively [20]. Calculating the sample size for detecting non‐inferiority with a power of 0.90 and alpha of 0.05, and a non‐inferiority margin of 2%, a sample size of 230 patients is needed. To account for missing or poor‐quality recordings, and drop‐out, we aim to recruit 300 patients.

We will calculate the sensitivity, specificity, negative predictive value (NPV), positive predictive value (PPV), and positive (LR+) and negative (LR−) likelihood ratios with 95% CI for both methods. We will use McNemar's test to compare the two methods.

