In the STEPCARE trial, 50% of the patients are randomized to minimal sedation, which allows a proportion of patients with good functional outcomes to wake up early, in some cases even before 12 h post‐arrest. Thus, some patients may not be included in the current study. However, we expect that most patients in the minimal sedation group and all patients in the deep sedation group will be unconscious at 12 h after ROSC. Further, awake patients obeying commands usually have a good functional outcome and thus do not require neuroprognostication. Although multimodal prognostication occurs in a later phase, an early prognostication may provide valuable information, especially for avoiding inadequate withdrawal of care in the future and encouraging continued care in patients with late awakening. As previous knowledge on the performance of the C‐Trend Index in outcome prediction is obtained from patients under sedation [10, 11], assessing the performance of the C‐Trend Index in patients allocated to minimal sedation is also important.

The strengths of this study include the prospective multicenter design with a blinded analysis of the cEEG, a comparison of the C‐Trend Index with a gold standard, and a large patient population with an a priori calculation of the sample size needed to detect at least a 10% difference in accuracy.

The limited number of participating centres in the STEPCARE trial, due to the special equipment required for cEEG recording, may influence the generalizability of the results.

In conclusion, we will compare the predictive accuracy of the C‐Trend numerical index based on EEG SWA with visual assessment of cEEG in predicting favorable functional outcome 6 months after OHCA. We will also assess the effect of the sedation intervention on the predictive accuracy of the C‐Trend Index. If the C‐Trend Index is shown to be non‐inferior in predicting favorable functional outcome, it may provide a valuable information for decision making for ICU clinical staff at an early phase in a dynamic numerical form.

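### The sedation question is set on overall accuracy, where changes in sensitivity and specificity can offset, so unchanged accuracy would not show that the C-Trend cut-off of 20 transfers between sedation arms

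*Protocol article*

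**What the plan says.** All references are to the protocol article.

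- **Question (2.5).** Is the accuracy of the C-Trend Index and "visual analysis of cEEG in predicting favorable outcome affected by the sedation intervention of the STEPCARE trial"?
- **Hypothesis (1, Background and Significance).** The authors expect that "the accuracy will not be impaired by the sedation intervention".
- **Metric (2.9).** Accuracy is "calculated according to a formula (TP + TN)/(TP + TN + FP + FN"), the share of all patients who are classified correctly.
- **Cut-off (1).** The primary objective compares the C-Trend "Index cutoff value 20 with blinded retrospective visual analysis of cEEG". No separate cut-off by sedation arm is given.
- **Index and sedation (2.8, 4).** The index runs from 0 to 100, "with higher values referring to higher normal SWA seen during propofol sedation". The Discussion adds that earlier knowledge of the C-Trend "Index in outcome prediction is obtained from patients under sedation", and gives this as the reason why testing it under minimal sedation is important.
- **Other measures (2.6, 2.9).** Sensitivity, specificity, predictive values and likelihood ratios are planned for both methods, and sensitivity and specificity at cut-offs of 20, 50 and 80. None is tied to the sedation arms. The one test named, McNemar's, compares the two methods, not the two arms.

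**The concern.** The index is described by reference to slow waves under propofol, and its track record comes from sedated patients. An obvious way for it to fail under minimal sedation is that its values move while the cut-off stays at 20. If values fall in both outcome groups, more favorable-outcome patients drop below 20 (lower sensitivity) and fewer unfavorable-outcome patients stay above it (higher specificity). At the plan's 50% prevalence, accuracy is the plain average of the two, so a loss in one can be made up by a gain in the other.

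At stake is the reading of a null result. Similar accuracy in the two arms would appear to confirm the hypothesis and to support one cut-off for both regimens, even if the number of missed favorable-outcome patients had changed severalfold. The Discussion values the early signal partly for identifying patients with potential for recovery and for avoiding inadequate withdrawal of care. For those uses the two kinds of error are not interchangeable.

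**Working it through.** **Inputs from the article**
- Operating point at cut-off 20 (section 1): specificity 95% and sensitivity 83% for unfavorable outcome. Read for favorable outcome, this is sensitivity 95% and specificity 83%.
- Prevalence of favorable outcome 50%, 230 patients needed, 300 recruited (2.9).
- Half of the patients allocated to minimal sedation (4), so 230/2 = 115 per arm and about 57.5 per outcome group within an arm.

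**The plan's own figures.** Visual accuracy is (63.2 + 82.1)/2 = 72.65%, stated as 72.7%. For two independent proportions with one-sided alpha 0.05 and power 0.90, (1.645 + 1.282)² × (0.727 × 0.273 + 0.8608 × 0.1392)/(0.8608 − 0.727 + 0.02)² = 115.2 per group, or 2 × 115 = 230. The stated number reproduces; here it only supplies the size of each arm.

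**Assumptions, not in the article.** The index is normal with equal spread in each outcome group, and minimal sedation shifts it down by d SD. Then
- sensitivity = Φ(1.645 − d), because z(0.95) = 1.645
- specificity = Φ(0.954 + d), because z(0.83) = 0.954
- accuracy = (sensitivity + specificity)/2

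Example, d = 1: sensitivity Φ(0.645) = 74.0%, specificity Φ(1.954) = 97.5%, accuracy 85.8%.

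**Power, two-sided 5%, normal approximation.** Accuracy: two proportions with 115 per arm. Joint test: the sum of the two squared z values on 2 df (critical value 5.99), with noncentrality Σ (difference)²/[2p̄(1 − p̄)/57.5]. At d = 0.69 each term is 0.12²/(2 × 0.89 × 0.11/57.5) = 4.23, so the noncentrality is 8.46 and power is 74%.

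| Assumed shift under minimal sedation | Sens. | Spec. | Accuracy | Power, accuracy | Power, joint |
|---|---|---|---|---|---|
| None (deep-sedation reference) | 95.0 | 83.0 | 89.0 | – | – |
| Both groups down 0.69 SD | 83.0 | 95.0 | 89.0 | 5% | 74% |
| Both groups down 1 SD | 74.0 | 97.5 | 85.8 | 11% | 96% |
| Both groups down 1.5 SD | 55.8 | 99.3 | 77.5 | 65% | nearly 100% |
| Favorable down 0.75 SD, unfavorable down half as much | 81.5 | 90.8 | 86.1 | 10% | 63% |
| Only favorable down 0.75 SD | 81.5 | 83.0 | 82.2 | 31% | 51% |
| Both groups up 0.5 SD | 98.4 | 67.5 | 83.0 | 26% | 48% |
| Both groups up 1 SD | 99.6 | 48.2 | 73.9 | 84% | 97% |

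At 0.69 SD, missed favorable-outcome patients rise from 5% to 17% and false favorable calls fall from 17% to 5%, with accuracy unchanged. At 1 SD, a 21-point loss of sensitivity costs 3.2 points of accuracy.

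**Precision.** The 95% half-width of the between-arm difference in accuracy is 1.96 × √(2 × 0.89 × 0.11/115) = 8.1 points. For a single difference in sensitivity (95% against 83%) it is 1.96 × √[(0.95 × 0.05 + 0.83 × 0.17)/57.5] = 11.2 points.

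**The case against.** **The offset is assumed.** A reader might infer that sedation will make sensitivity and specificity cancel, so that the plan is bound to report no effect. The documents do not support that. They give no index distribution and no sedation effect. The 0.69 SD shift is the single non-zero point at which the two values swap exactly, so the 5% power there follows by construction. With 83% of unfavorable-outcome patients already below 20, sedation may mainly move the favorable group; accuracy then falls and has some power to show it. Large or upward shifts also show up in accuracy. This stands, and it limits the point to saying that the changes can offset. The point does not need exact offset, though: the joint comparison had more power in every scenario tried.

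**The anchor is soft.** The 95%/83% figures come from a smaller study, for a period before 12 h, with an interval of 83% to 100% around the 95%. At 50% prevalence they imply 89.0% accuracy, not the plan's 86.08%. This also stands; the figures illustrate and do not predict.

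**Only C-Trend is shown.** The mechanism is a numeric index moving against a cut-off. A reader might extend it to visual cEEG, but nothing in the article demonstrates it there.

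**The rest may be planned elsewhere.** The abstract speaks more broadly of performance, section 2 commits to STARD reporting, and the presentation of results is in Supporting Information that is not at hand. By-arm tables may well be foreseen, and their absence from an article is no error. What remains is that the question and the hypothesis, as stated, both name accuracy; an analysis plan that follows them would answer on that metric.

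**Conclusion.** The point holds as a weakness in a stated metric. Accuracy pools the two error rates that a moving index would change in opposite directions, and nothing in the article ties either rate to the sedation arms. Equal accuracy in the two arms would therefore not show that the cut-off of 20 transfers.

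The size cannot be fixed from the documents. Over the scenarios tried at 50% prevalence, power on accuracy ran from 5% to 84%, against 48% to nearly 100% for the joint comparison of the same patients. These figures rest on the binormal shape, the 95%/83% anchor, 115 analysed per arm and the assumed shifts. At 40% prevalence the joint comparison again had more power. The point concerns the secondary question for the C-Trend Index; it leaves the primary comparison of methods and its margin untouched.

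**What to change.** In sections 2.5 and 2.9:

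1. Answer the sedation question for the C-Trend Index at cut-off 20 by comparing sensitivity and specificity between the randomised sedation arms. Give each difference with its 95% CI, and one joint 2-df test.
2. Report the same by-arm figures for visual cEEG, for comparability.
3. Keep accuracy by arm as a summary.
4. State that a conclusion of not affected, or not impaired, will not be drawn from accuracy alone. Align the hypothesis in section 1 with this.

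The cost is wording only, with no new data or patients. The downside is that each single difference rests on about half of each arm, hence the wider interval of about 11 points against 8 for accuracy.

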### Other Study Questions

2.6

What is the prognostic value of C‐Trend Index in terms of sensitivity and specificity when using predefined cut‐off values above 50 and 80 in predicting favorable outcome?

What is the prognostic value of C‐Trend Index in terms of sensitivity and specificity when using a predefined cut‐off value below 20 to predict unfavorable outcome?

### Management and Study Procedures

2.7

The management in the ICU is according to the STEPCARE trial protocol [14, 16, 17, 18]. A cEEG recording on randomized patients will be initiated as soon as possible after admission to the ICU and continued at least 24 h from ROSC or until the patient awakens to obey verbal commands, whichever comes first. The recording is carried out with a disposable self‐adhesive BrainStatus electrode (Bittium Oyj, Oulu, Finland) attached to the forehead of the patient, including 10 EEG electrodes on positions Fp1, Fp2, Af7, Af8, F7, F8, Sp1, Sp2, T9, and T10, and a wireless BrainStatus recording device (Bittium Oyj, Oulu, Finland). The treating clinical team can decide whether to add more EEG electrodes in addition to the BrainStatus electrode when monitoring cEEG or the performance of intermittent routine EEGs. Electrode placement and initiation of recording are performed according to written instructions.

### Data Extraction

2.8

Original raw EEG signals are displayed on a bedside monitor at sites that use cEEG for routine monitoring of cardiac arrest patients and may be used as part of the multimodal prognostication defined in the STEPCARE protocol. The cEEG data are stored on a bedside computer or hospital server during the recording. The cEEG data are then pseudonymized before blinded retrospective analysis ([name]). Amplitude‐integrated EEG and basic spectrogram analysis can be used to aid the retrospective visual analysis, but no other computational methods will be used. All cEEGs will be assessed by two out of three raters, according to the ACNS 2021 criteria [19], and inconsistencies between raters will be resolved by the third rater. The best EEG background pattern, present for at least five consecutive minutes, will be obtained in the hour between 11 and 12 h after CA. If recording quality is insufficient for visual analysis, the hour with the best recording quality closest to 12 h (12 h ± 3 h) after CA is used. At least 1 h of EEG recording with sufficient recording quality is required to be included in the analysis. cEEG analysis is performed by investigators blinded to the clinical outcome data and intervention group allocation after the recording of the last study participant has been finished. To minimize the risk of uncovering the allocated intervention, the cEEG recordings are accessible only for up to 15 h to the investigators performing the analysis. In all centres, including those using visible cEEG monitoring data for clinical purposes, treatment decisions on withdrawal of life support are based on ERC/ESICM guidelines [1], and strictly determined by the STEPCARE protocol [14, 16, 17, 18].

The C‐Trend Index values are calculated offline after the recording. The parameter is provided by C‐Trend (Cerenion, Oulu, Finland), a CE‐marked medical device software that utilizes artificial intelligence to capture several power and connectivity features in producing the C‐Trend Index. The parameter ranges from 0 to 100 in values, with higher values referring to higher normal SWA seen during propofol sedation. The parameter is not displayed on the bedside monitor and is not used during the clinical review of the cEEG data. Thus, all clinical and research personnel are blinded to the C‐Trend Index. A running 1‐h average value of the C‐Trend Index is automatically calculated, and for the analysis, the value is picked for each patient from the same time location used in the visual analysis of cEEG.

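### The 15 h limit on rater access is not restricted to recordings that need the fallback hour, so visual readers may see a cue to outcome and sedation arm that C-Trend cannot use

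*Protocol article*

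**What the plan says.** All of this is in the protocol article.

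- **Rated hour (Data Extraction, 2.8).** The best background pattern "will be obtained in the hour between 11 and 12 h after CA".
- **Fallback (2.8).** "If recording quality is insufficient for visual analysis, the hour with the best recording quality closest to 12 h" is used instead, within 12 h ± 3 h, that is, 9–15 h.
- **Access limit (2.8).** The rule is that "the cEEG recordings are accessible only for up to 15 h to the investigators performing the analysis". The natural reading is 15 h after the arrest, because that is where the fallback window ends. The only purpose given for the rule is "To minimize the risk of uncovering the allocated intervention".
- **Blinding (2.8).** "cEEG analysis is performed by investigators blinded to the clinical outcome data and intervention group allocation".
- **End of recording (Management and Study Procedures, 2.7).** Recording runs for at least 24 h from ROSC "or until the patient awakens to obey verbal commands, whichever comes first".
- **Awakening (Discussion, 4).** Half of the patients are allocated to minimal sedation, "which allows a proportion of patients with good functional outcomes to wake up early". The Discussion expects every deep-sedation patient to be unconscious at 12 h, and says that patients who obey commands mostly do well.
- **C-Trend (2.8).** The index is an automatic 1-h average, taken at the time location chosen for the visual reading.

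**The concern.** The access limit is wider than the normal reading task needs. If the 11–12 h hour is usable, nothing after 12 h is required, yet the stated rule lets raters look on to 15 h. In those hours a trace may stop, or show waking, because the patient has begun to obey commands. On the article's own account this makes a good outcome and the minimal-sedation arm more likely.

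The comparison is paired, and the two methods would not have the same information. C-Trend is fixed to one hour, whereas a human reader can be influenced by what comes next. The limit is justified only as protection against uncovering the intervention. It does not address leakage of outcome, although the raters are declared blinded to both.

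Two things are at stake. The primary question (2.4) sets C-Trend against a blinded visual reading with a 2-point margin. The secondary question (2.5) asks whether the sedation arm changes the accuracy of each method, and early wakers are expected mainly in one arm.

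**Working it through.** **Inputs from the article (Statistical Analysis Plan and Data Analysis, 2.9).** Visual sensitivity is 63.2%, specificity 82.1%, favourable prevalence 50%, C-Trend accuracy 86.08%, margin 2 points, power 0.90, alpha 0.05 and N = 230.

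**Assumed inputs (not in the article).**
- *s*: the share of all patients whose trace ends or shows waking at 12–15 h. Assumed 5%, range 2–10%, with all of them having a favourable outcome.
- *q*: the share of otherwise missed readings in these patients that would change to favourable. The upper bound is q = 1.

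**Step 1: reproduce the plan's figures.** Visual accuracy = (0.632 + 0.821)/2 = 0.7265, the stated 72.7%. For non-inferiority of two independent proportions at one-sided alpha 0.05:

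n per group = (1.645 + 1.282)² × [0.7265 × 0.2735 + 0.8608 × 0.1392] / (0.8608 − 0.7265 + 0.02)² = 114.6, rounded up to 115, so 2 × 115 = 230. The stated N is reproduced.

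**Step 2: excess exposure.** The normal reading ends at 12 h and access ends at 15 h, so up to 3 hours are visible that the reading does not need.

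**Step 3: largest shift in visual accuracy.** The miss rate among favourable patients is 1 − 0.632 = 0.368, so the shift = s × 0.368 × q. With q = 1:

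| s | Patients of 230 | Of whom missed (× 0.368) | Shift in visual accuracy |
|---|---|---|---|
| 2% | 4.6 | 1.7 | 0.7 points |
| 5% | 11.5 | 4.2 | 1.8 points |
| 10% | 23 | 8.5 | 3.7 points |

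The margin is 0.02 × 230 = 4.6 patients. With q = 0.5 every shift halves. A shift of the full 2 points needs s × q = 0.02/0.368 = 0.054.

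**Step 4: power on the plan's own basis** (115 per group, one-sided 0.05, q = 1). With s = 5%, visual accuracy becomes 0.7449 and power falls from 0.90 to 0.84. With s = 10%, accuracy becomes 0.7633 and power 0.74. If instead all 230 patients are read by both methods with independent errors, power is 0.98 and 0.95 respectively.

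**Step 5: secondary comparison.** If all the wakers are in one arm of 115, the same missed patients amount to 1.7/115 = 1.5 points, 4.2/115 = 3.7 points and 8.5/115 = 7.4 points of that arm's visual accuracy.

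**Step 6: plausibility of the range.** Favourable, minimal-sedation patients number about 230 × 0.5 × 0.5 = 57.5. If all wakers come from this group, s = 2%, 5% and 10% mean that 8%, 20% and 40% of it wake within one 3-hour window. The top of the range is demanding.

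**The case against.** The strongest defence is that the limit is reasoned. Choosing the best hour nearest 12 h requires sight of the window up to 15 h, and the limit keeps raters from seeing the remainder of a recording of 24 h or more. It is also an upper bound, which is compatible with staged release described in a fuller document. Both points are fair. What remains is that the printed rule does not confine the later hours to recordings that need the fallback.

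A reader might infer that a truncated trace reveals outcome and arm, so that the readers are in effect unblinded. The article does not support this. A trace can also stop because of death, electrode or device failure, or transfer, and nothing says that raters are told the reason. The Discussion's statements about waking and outcome concern some patients and the usual case, so the cue is only probabilistic.

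Raters also do not predict outcome. They code a background pattern of at least five minutes in a defined hour by ACNS 2021 criteria, with two of three raters reading and the third resolving disagreement. This limits the influence of later trace without removing it.

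The arithmetic in Step 3 leans high. It applies the average miss rate of 36.8% to patients about to wake, who may well be missed less often, and it lets every missed reading change.

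Finally, the direction is conservative for the primary claim. A leak that raises visual accuracy makes non-inferiority of C-Trend harder to show.

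**Conclusion.** The point holds as a modest, avoidable weakness in the blinding. The stated access rule leaves visual readers a probabilistic cue to outcome and arm at 12–15 h that C-Trend cannot use.

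Its size cannot be derived from the article. The upper bound is about 0.7–3.7 points of visual accuracy, for assumed waking shares of 2–10% of all patients, a 36.8% miss rate and every missed reading changed. The real effect is smaller if any of these is too generous.

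A reader might go further and conclude that the primary comparison is undermined or that C-Trend could falsely pass. That does not follow: the bias works against C-Trend, and the planned advantage is 86.08 − 72.65 = 13.4 points. The cost there is some power. The sedation-arm comparison has no such protection, because a leak concentrated in one arm could create or hide a difference in visual accuracy.

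**What to change.** At the existing pseudonymisation step, crop each file so that raters first receive only the 11–12 h hour, and hide the recording end time. Raters grade whether that hour is sufficient, and the grading is locked. Only when it is graded insufficient are the other hours within 12 h ± 3 h released. State this rule in place of the general 15 h limit. Reading is planned to begin only after the last participant's recording has finished, so one rule can cover every file.

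The cost is file cropping at a step that already exists and a second release for poor-quality recordings. No extra patients or readers are needed, and C-Trend, computed offline, is unaffected.

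Two limits remain. Sedation effects within the rated hour will still be visible, so masking of allocation is improved but not complete. Recordings that go to the fallback keep some exposure to the later hours.
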